***Outcomes measured*:**

The primary endpoint will be combined all-cause mortality (ACM) or unplanned cardiovascular (CV) hospitalisation whichever came first.

The Endpoint Review Committee will adjudicate on :

1. the appropriate classification of cause of death, using data from primary and secondary care records, coroner reports and the death certificates. Mortality data will be obtained from the NHS Medical Research Information Service (MRIS)
2. underlying cause of hospitalisation using a standardised proforma and reviewing circumstances of hospitalisation from primary care records and hospital notes.

Secondary outcomes will include ACM, unplanned CV hospitalisation, CV mortality, unplanned CV hospitalisation, and unplanned hospitalisation.

*Quality of Life Assessment:* All participants will complete the SF-12, EuroQol (EQ5D), and Kansas Heart Failure Questionnaire (KHFQ) at enrolment, 3 months, 6 months, 12 months and 24 months. These will be administered by the study remote monitors. The initial quality of life forms will be completed at the time of patient enrolment in the hospital. Subsequent assessments will be performed by the patients in their homes. The forms will be sent to them by post with the necessary means for return of the forms. Receipt of the forms and their return will be managed by the remote monitors and local study administration staff. *Cost-effectiveness:* including cost of interventions, cost of Cardiovascular related health care.

Process measures will be collected to compare the pattern of care between the two arms and across centres (as we have no standardisation of usual care and the protocol is a pragmatic guideline and interpretation may differ between centres).

Key abnormalities detected in RM relate to atrial/ventricular arrhythmias and HF events. Key interventions are medication patterns, including anti-coagulation for atrial fibrillation.

There will be assessment of implementation of recommended interventions in the RM group and particularly those performed in primary care.

This flow chart summarises the study:

*- Acute care*

In the event of symptomatic deterioration, patients in the remote management arm will be instructed to contact the heart failure study nurse according to local practice or remote monitor during office hours and to perform an immediate data download. The remote monitor will report in a prompt manner to the patient that the download has been received and will give the patient a management plan. This plan will be documented on the patient’s record. Execution of the management plan will be the responsibility of the primary care team and the remote monitor will communicate the plan during office hours on the day of the download to the primary care physician or his/her deputy with responsibility for that patient, so that clinical care changes can be implemented during the same working day. The primary care clinician will be asked to document receipt of that information and execution of a management change. In the event that the primary care clinician suggests an alternative plan then this will be communicated to the remote monitor.

*- Emergency care*

In the event of a clinical emergency or urgent out of hours/weekend deterioration the patient will access the emergency services in the usual way. However, the patient can be issued with a study identity card for presentation to clinical staff caring for the patient on hospital admission. This card will identify ways of downloading data to the remote monitor so that data relating to the emergency admission is captured in study records. It will not be used to guide emergency management.

**10 Data Analysis**

**Outcomes measured will be:**

**Primary endpoint:** Combined endpoint of all cause mortality or unplanned hospital admission for any cardiovascular event

**Secondary endpoints:** Quality of life using the EuroQol (EQ5D), SF12 (using physical and mental health component scale) and Kansas Heart failure questionnaire at 1 and 2 years.

Using survival analysis we will consider:

- ACM
- CV mortality
- Unplanned CV hospitalisation
- CV mortality or unplanned CV hospitalisation
- Cumulative number of unplanned CV hospitalisations using multinomial logistic regression (0,1,2,>2)

For harm see below under interim analyses: ACM and any unplanned hospitalisation.

**Costs**

Costs of both implanted devices and conventional heart failure monitoring will be measured. These will include the costs associated with dealing with data obtained. Also measured will be all costs associated with providing heart failure related care in both arms of the study.

***Sample size calculations:*** Our sample size calculations use estimates from previous studies: i) Intervention group event rate: The Companion^38^ and Care HF^39^ trials with a patient population comparable to our study control group, reported 48% for any death or cardiovascular disease hospitalisation at 2 years, and 39% at 29 months for cardiovascular death or unplanned hospitalisation. We anticipate slightly lower rates in the proposed due to their receiving better routine care, and so assume a 40% event rate in the control arm by 2 years. ii) Overall risk reduction: The meta-analysis of Clark et al^10^ with telemonitoring or structured telephone support, reported a 20% risk reduction. Hence we will assume that the intervention group has a rate of 32%. This size of effect (40% reduced to32%) is clinically relevant. Assuming 5% (2-sided) significance and 90% power, 546 events are needed to detect this size of difference in a log-rank survival comparison of the two trial groups. This requires 1394 patients in total (697 per group). We will inflate this total by approximately 20% to allow for attrition, giving a target recruitment of 1650. This sample size is sufficient to estimate the effect size in the component outcomes - ACM, cardiovascular disease unplanned hospitalisation - and is feasible.

***Statistical analysis:***

Cox proportional hazards regression will be used to analyse the primary outcome data according to the intention to treat. The stratifying variables will be entered as covariates and any clinically important baseline imbalance will also be accommodated in the model. Estimates will be reported as hazard ratios with 95% confidence intervals. Secondary clinical outcomes with time to event will be analysed in a similar way using a multifactorial survival analysis modelling method appropriate to the multicentre nature of the data (i.e. to allow for centre effects).

We will censor at time at study end for those alive and free of hospitalisation and at last date known to be free of hospitalisation for those who are lost to follow-up (e.g. leave the area). Withdrawals from RM will be recorded but such will be analysed at ITT.

Quality of life outcomes will be analysed at 1 and at 2 years.

From Euroqol : utility, VAS.

From SF12: Utility; Mental component score (MCS); Physical component score (PCS)

Kansas Heart failure numerical score.

Results will be analysed by multiple or logistic (if pre-specified categories) regression. Multiple imputation will be used to explore the impact of missing data in QoL data.

Cumulative number of unplanned CV hospitalisations will be analysed by multinomial logistic regression

A priori sub group analysis for the primary outcome will be conducted on the following variables:

Age

History of atrial fibrillation

Type of device (ICD, CRT-P,CRT –D)

Baseline functional status (NYHA grade, Kansas HF score).

***Interim analysis:***

We propose that the Independent Monitoring Committee (IMC) will review recruitment, data completeness and end points, and ensure no adverse effects from remote monitoring, at appropriate time points during the study.

For benefit we will use the primary outcome and Peto–Haybittle rule which uses a p value of p<0.001This is recommended by Pocock (Pocock SJ, Current controversies in data monitoring for clinical trials Clin Trials 2006;3:513e21) as it is conservative, would likely lead to a recommendation to stop only when there is a very convincing effect, thus preventing premature stopping of the trial, and it does not affect final analysis p values (final would be p=0.048) .

We plan one interim analysis based on primary events accumulated (at approximately 400 events).

For harm key outcomes will be ACM and any unplanned hospitalisation (e.g. if RM leads to over zealous use of diuretics leading to falls, acute renal failure) and we plan to undertake this interim analysis at the same time as benefit analysis.

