***Strategy*:**

*Step 1:* Initiate appropriate anticoagulation regime.

*Step 2:* Consider device programming.

a) Therapy for AF may affect device parameters. Consider detection and discrimination parameters and discuss with technician staff. In particular decided whether the rate is sufficiently fast to:

- Satisfy the VT/VF detection rate and lead to inappropriate shocks?
- Inhibit biventricular pacing?

Again answer to these questions may require discussion with technical staff and cardiology consultant. If in doubt consult them.

1. Therapy for AF may affect patient surveillance. If this is newly diagnosed and the patient is asymptomatic then increase frequency of downloads to twice weekly (and discuss with supervising cardiologist) for 4 weeks until the clinical situation is clearer. As a simple rule, if this is newly diagnosed atrial fibrillation and a remote treatment change is instituted, then increase the frequency of follow up to weekly for 4 weeks post management change.

*Step 3:* Consider treatment plan which may be:

- Rate control scenario
- Rhythm control scenario

A decision needs to be made as to what is the long-term rhythm control aim.

The decision could be determined by a number of clinical features and should be discussed with the supervising consultant who can make an informed decision about the overall direction of treatment strategy. This will not need face-to-face patient encounters although implementation of the chosen clinical strategy may do so. It will be influenced strongly by the atrial fibrillation classification. Thus, your task to is to “classify” the atrial fibrillation and then consider with the supervising physician a treatment plan.

Rhythm Control: Paroxysmal Self Terminating Atrial Fibrillation

In this instance rhythm control strategy will be adopted. If amiodarone is commenced consider the possible effect of this drug on defibrillation efficacy (see below). There is relatively less experience of the use of dronedarone in this scenario but if it is suggested by the responsible physician ensure that surveillance is maintained according to developing standards. Selection of any other antiarrhythmic drugs should follow careful clinical discussion.

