### 3.2.2 Secondary Endpoints

The secondary endpoints of the trial are:

1. Time to death.
2. Time to a cardiovascular related death.
3. Time to a non-cardiovascular related death.
4. Time to first unplanned hospitalisation for cardiovascular reasons or cardiovascular related death.
5. Time to first unplanned hospitalisation for non-cardiovascular reasons or death by any cause.
6. Time to first unplanned hospitalisation for cardiovascular reasons.
7. Time to first unplanned hospitalisation for non-cardiovascular reasons.
8. Total number of unplanned hospitalisations.
9. Total number of unplanned hospitalisations for cardiovascular reasons.
10. Change from baseline in SF12 scores at 2 years (physical and mental health components).
11. Change from baseline in EQ5D scores at 2 years.
12. Change from baseline in KCCQ at 2 years.
13. Change from baseline in SF12 scores at 1 year (physical and mental health components).
14. Change from baseline in EQ5D scores at 1 year.
15. Change from baseline in KCCQ at 1 year.
16. Number and cost of hospitalisations.
17. Difference in cost of resources consumed.
18. Difference in cost of cardiovascular related health care use.
19. Incremental costs per quality-adjusted life years (QALYs).

Unless otherwise stated, secondary endpoints will be measured at the last follow-up or at the last available observation within the two year follow-up period.

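### The interim harm look pools the cardiovascular admissions the intervention should reduce with the over-diuresis admissions it should detect; adding the split and cause-specific counts by arm is a cheap improvement

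*Combined protocol and SAP*

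**What the plan says.** Protocol section 10 names the harm outcomes twice. The endpoint list says "For harm see below under interim analyses: ACM and any unplanned hospitalisation", and the interim analysis text says "For harm key outcomes will be ACM and any unplanned hospitalisation (e.g. if RM leads to over zealous use of diuretics leading to falls", with acute renal failure as the other example. The harm look takes place with the benefit look: "We plan one interim analysis based on primary events accumulated (at approximately 400 events". No harm threshold is given.

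SAP 2.5.1 says the interim concentrated on safety and the primary outcome, and names no harm outcome. SAP 3.2.2 lists "Time to first unplanned hospitalisation for non-cardiovascular reasons" as a secondary endpoint (item 7). Item 5 is the same event combined with death, and items 8 and 9 are total and CV unplanned admissions. None of these is assigned to the interim harm look.

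The Endpoint Review Committee (ERC) charter, SAP 7.1, counts symptomatic hypotension linked to heart failure medication, and significant renal or metabolic disturbance linked to heart failure or its medication, as CV admissions for heart failure. Syncope and pre-syncope without signs of heart failure or withdrawal of heart failure medication are CV admissions not for heart failure.

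**The concern.** Unplanned CV admissions are part of the primary endpoint, and the trial is sized on that endpoint falling from 40% to 32% at two years. The same admissions sit inside the hospitalisation outcome meant to reveal over-treatment. The pooled hazard ratio is therefore a weighted average of an expected benefit and a possible harm, and the better the intervention works, the less a given harm shows.

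At stake is whether the monitoring committee is routinely shown a comparison that responds to the harm the protocol names. Hospitalisation carries much of the safety information here, because SAP 5.1 states that adverse events are not actively collected.

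**Working it through.** **1. The plan's own figure.** The plan says "assume a 40% event rate in the control arm by 2 years" and 32% with the intervention, so HR = ln(0.68)/ln(0.60) = 0.755. It also says "Assuming 5% (2-sided) significance and 90% power, 546 events are needed". Schoenfeld: 4 × (1.960 + 1.282)² / (ln 0.755)² gives 533. Freedman: (1.960 + 1.282)² × [(1 + 0.755)/(1 − 0.755)]² gives 540. Both are within 3% of 546, so 0.755 is the planned effect.

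**2. Timing of the look.** Monthly primary hazards are −ln(0.60)/24 = 0.02128 (control) and −ln(0.68)/24 = 0.01607 (intervention). With 1650 patients, 825 per arm, entering uniformly over months 2–24 (my reading of the timetable), the 400th primary event falls at month 28.3.

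**3. Assumptions not in the documents.**
- CV admissions are 75% of the control primary hazard: 0.75 × 0.02128 = 0.01596 per month, with HR 0.755.
- Two-year mortality is 15%: −ln(0.85)/24 = 0.00677 per month.
- The control non-CV admission hazard is r × 0.01596 with r = 0.5, 1 or 1.5. Two-year non-CV risk, 1 − exp(−24 × r × 0.01596), is then 17%, 32% or 44%.
- A harm signal is p < 0.05, two-sided, in the harm direction.

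**4. Formulas.** With h the true HR for non-CV admissions:
- pooled HR = (0.755 + h × r)/(1 + r), replacing 0.755 by 1 if there is no CV benefit;
- first events per arm = 825 × the average over entry month e of [λ/(λ + 0.00677)] × {1 − exp[−(λ + 0.00677)(28.3 − e)]}, where λ is the admission hazard;
- chance of a signal = Φ(ln HR × √D / 2 − 1.96), where D is first events in both arms.

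Example, h = 1.3 and r = 1. Pooled HR = (0.755 + 1.3)/2 = 1.03 (1.0275 unrounded) with D = 591: Φ(0.33 − 1.96) = 5%. Non-CV alone, D = 373: Φ(2.53 − 1.96) = 72%.

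**5. Results for r = 0.5 / 1 / 1.5.**

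| True non-CV rise | CV effect | Pooled HR | Chance, pooled | Chance, non-CV alone |
|---|---|---|---|---|
| 30% | HR 0.755 | 0.94 / 1.03 / 1.08 | 0.4% / 5% / 18% | 46% / 72% / 85% |
| 30% | none | 1.10 / 1.15 / 1.18 | 18% / 41% / 61% | as above |
| 50% | HR 0.755 | 1.00 / 1.13 / 1.20 | 3% / 32% / 70% | 85% / 98% / over 99% |
| 50% | none | 1.17 / 1.25 / 1.30 | 40% / 80% / 95% | as above |
| 100% | HR 0.755 | 1.17 / 1.38 / 1.50 | 42% / 98% / about 100% | about 100% |

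**6. Cross-check with other inputs.** The pooled HR equals 1.00 when the non-CV HR is 1 + (CV hazard, control − CV hazard, intervention)/(control non-CV hazard). With a 40% two-year CV rate and a 20% non-CV rate this is 1 + (0.2554 − 0.1928)/0.1116 = 1.56, in yearly hazards. Over CV rates of 30–40% and non-CV rates of 10–40%, the break-even runs from 1.17 to 2.19.

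**7. Effect of the ERC labels.** Suppose half of the excess behind the 30% rise is coded CV. The non-CV HR falls to 1.15 and the chance of a signal on non-CV admissions to about 16% / 26% / 34%. If three quarters is coded CV, the HR is 1.075 and the chance about 7% / 10% / 12%. Both shares are assumptions.

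**The case against.** A net measure is a legitimate safety outcome: when total admissions are flat, it should read neutral. It also captures an admission under any label, which a non-CV outcome would not. The committee is unblinded and sees the primary outcome and safety together, so a pooled ratio near 1 beside a lower primary event rate would itself point to an excess elsewhere. Its charter (SAP 7.2) lets it request further data. For the final analysis, SAP 3.2.2 and planned Table 5 already separate non-CV admissions, and SAP 5.3 tabulates serious adverse events by pathway.

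Most of this stands. It is why the pooled outcome should stay and why this is an improvement rather than a serious flaw. It does not remove the gap. A data request is discretionary, the adverse event tables are split by relatedness with no planned comparison between arms, and a net measure alone does not answer the protocol's aim of ensuring that monitoring has no adverse effects.

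A reader might also count bleeding among the masked harms, since Appendix II tells monitors "Initiate appropriate anticoagulation regime" when atrial fibrillation is found. The harm text does not mention bleeding, and the documents do not show how it would be classified, so the point rests on falls and renal failure.

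**Conclusion.** The point holds as a cheap improvement. The only hospitalisation outcome named for the interim harm look contains the events the intervention should prevent. Under the full planned benefit, a 30% rise in non-CV admissions would give a harm signal 0.4% to 18% of the time on the pooled outcome, against 46% to 85% on non-CV admissions. This rests on the assumed r, 75% CV share, 15% mortality and 5% harm test, and on all of the excess being coded non-CV.

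Two stronger readings are tempting. One is that the pooled outcome cannot show harm. The table contradicts it: with no CV benefit a 50% rise is detected 40% to 95% of the time, and a doubling at r = 1 or more is detected at least 98% of the time even with the benefit. The other is that non-CV hospitalisation should replace the pooled outcome. The ERC charter rules that out, because several over-diuresis admissions count as CV and so as primary events.

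**What to change.** In protocol section 10 and SAP 2.5.1, keep all-cause mortality and any unplanned hospitalisation (as the net effect) as harm outcomes. Add to the interim report, by arm:

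- unplanned CV and unplanned non-CV hospitalisation shown separately, as first event and as total;
- unplanned admissions for falls or syncope, renal or metabolic disturbance, and symptomatic hypotension, counted whatever their ERC label.

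In the final analysis, first non-CV hospitalisation is already covered (endpoints 5 and 7) and total non-CV admissions follow from endpoints 8 and 9, so only the cause-specific rows are new. SAP 2.5.1 describes the interim in the past tense; if that look is complete, the rows can still go in the final safety report.

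The cost is wording and a few table rows. Admissions are already adjudicated, and serious adverse events are to be MedDRA-coded. The downside is a few more safety comparisons, with a slightly higher chance of a false safety signal. The efficacy significance level is unaffected.

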**11 Cost Effectiveness**

The outcome measure used in the economic evaluation will be cost per quality adjusted life years (QALY). QALYs will be estimated using the EuroQol (EQ5D). Costs will be measured using an NHS perspective. As part of the study we will record the costs associated with providing remote monitoring, as well as any routine cardiac care received in each group. Resource use will be obtained from a variety of sources as appropriate, including hospital records and directly from participants. Where possible we will follow published guidelines for cost-effectiveness analysis, for example the NICE reference case and the BMJ guidelines for authors of economic evaluations.

**12 Training**

*Remote Monitoring Preparation*

Patients will be introduced to the remote monitor providing remote care and will be instructed in use of the care pathways.

Patients will receive training on use of remote monitoring through their implanted device by the study site remote monitor. They will receive their home monitoring transmission devices (specific model depending on implant device features). Devices will be interrogated using a monitor with automatic or manual download capabilities with either wireless or non wireless technology.

The remote monitor will communicate with the patients’ primary care services to inform them of entry to the study

**13 Project timetable:**

***STUDY TIME LINES:***

### Staff training & deployment

**Patient Follow-up**

**Data Analysis**

**Results Dissemination**

**Patient Recruitment**

**1-2**

**2-24**

**2-48**

**48-54**

**55-60**

**14 Data Storage**

For each enrolled patient, data will be stored in a specific study database. All aspects of local data recording and management will be performed by the remote monitor.

**15 Database**

An ECRF will be utilised to capture healthcare utilisation elements, QoL assessment and clinical events on a patient by patient basis allowing accurate and comprehensive assessment of care pathway. The Southampton Clinical Trials Unit is managing this. The data will be held by University Hospital Southampton NHS Foundation Trust and will conform to all Data Protection Requirements.

**16. Expected Value Of Results**

The NHS needs to develop different care mechanisms that enable effective use of technology to help better manage patients with chronic disease such as heart failure in the community, with safety, clinical efficacy, and overall patient benefit. We need to prove that the care model and technologies tested in this trial offer the potential for personalized health care through "remote" patient management in the community using secondary and tertiary care expertise and simple interventions as required. Our care model challenges usual patterns of healthcare delivery, bringing care and expertise closer to the patient. Dissemination of this technology in NHS care, in an optimal care pathway model, could greatly improve patient outcomes and the economics of CHF management, with planned therapy changes pre-empting symptomatic deterioration and the need for emergency hospitalisation, thus improving resource utilization. Improving health outcomes with reduced overall cost is needed more now than ever before, and this study may be an important step in that direction for the increasing number of people with heart failure who have an implanted device.

